## Additional hypotheses

1. When compared with performing systematic biopsies for men with elevated risk of prostate cancer in prostate cancer screening, targeted and systematic prostate biopsies performed on MRI positive men has non-inferior sensitivity for detecting clinically significant cancer (ISUP grade group  $\geq 2$ ) and reduces the number of performed biopsy procedures, which also translates to lower proportion of men with elevated risk who experience severe post-biopsy infections. Elevated risk can here be defined using PSA or S3M – we clarify the exact contrasts for testing this hypothesis below.
2. When compared with performing systematic biopsies for men with elevated risk of prostate cancer in prostate cancer screening, targeted biopsies only performed on MRI positive men has non-inferior sensitivity for detecting clinically significant cancer (ISUP grade group  $\geq 2$ ) and reduces the number of performed biopsy procedures, which also translates to lower proportion of men with elevated risk who experience severe post-biopsy infections. Elevated risk can here be defined using PSA or S3M – we will clarify the exact contrasts for testing this hypothesis below.
3. A diagnostic chain consisting of Stockholm3 followed by MRI and targeted+systematic biopsies (S3M+MRI+TBx+SBx) versus a diagnostic chain based on PSA  $\geq 3$  ng/ml followed by MRI and targeted+systematic biopsies (PSA+MRI+TBx+SBx) will lead to: non-inferior sensitivity for detecting clinically significant cancer (ISUP grade group  $\geq 2$ ); an inferior sensitivity for ISUP1 cancers (i.e. reduced overdiagnosis); and a reduction in the number of MRI examinations and performed biopsies.
4. A diagnostic pathway using the Stockholm3 test to select men for further workup using MRI followed by ONLY targeted biopsies (S3M+MRI+TBx) has non-inferior sensitivity for detecting clinically significant cancer (ISUP grade group  $\geq 2$ ) and reduces the number of performed biopsy procedures compared with a diagnostic pathway using systematic biopsies in men with PSA  $\geq 3$  ng/mL (PSA+SBx).
5. Biopsy compliance is higher after biopsy is recommended based on MRI compared to recommended without MRI.
6. SBx in the MRI arm has superior sensitivity than SBx in the non-MRI arm (due to cognitive fusion).
7. A diagnostic chain consisting of Stockholm3 followed by MRI and targeted+systematic biopsies (S3M+MRI+TBx+SBx) is cost-effective (ICER < 750 000 SEK per QALY gained) compared to a diagnostic chain based on PSA  $\geq 3$  ng/ml followed by MRI and targeted+systematic biopsies (PSA+MRI+TBx+SBx) due to reductions in number of performed procedures (men undergoing MRI and biopsy).
8. A diagnostic chain using the Stockholm3 test to select men for further workup using MRI and targeted+systematic biopsies (S3M+MRI+TBx+SBx) is cost-effective compared to a diagnostic chain using systematic biopsies in men with PSA  $\geq 3$  ng/ml (PSA+SBx).
9. Adding prostate volume as a variable in the diagnostic chain with Stockholm3 test (i.e. using the full Stockholm3 model described in Ström et al.) and MRI/Fusion biopsies improves model precision, leading to further improvements in specificity compared to the use of the Stockholm3 test without the inclusion of prostate volume.

## Publications strategy of main study results

A large number of publications will likely be written based on the data collected within the STHLM3MRI trial. The main study results from the trial will be reported in the two first publications:

## Publication 1

Publication 1 will as primary contrast report the comparison of Strategy 3 vs. 1 (PSA+MRI+TBx+SBx vs PSA+SBx). Additional analysis in the report will include contrasts of Strategies 2 vs 1.

This comparison uses only the randomized step of the trial design and is motivated by the need to provide level 1 evidence about the performance of MRI+targeted+systematic biopsies versus systematic biopsies alone in men with PSA  $\geq 3$  ng/ml in a screening-by-invitation context, where such data is lacking entirely. The choice of using systematic biopsies without MRI as the comparator hinges on the fact that, presently, this is the typical diagnostic strategy offered to men with an elevated PSA (Ahmed et al.). Furthermore, level 1 evidence about a mortality benefit from early detection of prostate cancer is available only for a diagnostic strategy based on PSA+systematic biopsies (Schröder et al. 2009 and 2014). Thus, Publication 1 will assess whether introducing PSA+MRI+TBx+SB into prostate cancer screening can diagnose clinically significant prostate cancer with non-inferior sensitivity to PSA+SB, for which there is level 1 evidence of a reduction in prostate cancer mortality. Publication 1 will cover additional hypotheses 1 and 2.

## Publication 2

Publication 2 will report the contrasts of Strategy 6 vs. 3 (S3M+TBx+SBx vs. PSA+TBx+SBx) and Strategy 6 vs. 1 (S3M+TBx+SBx vs. PSA+SBx), where the latter contrast corresponds to assessing the performance of the entire diagnostic chain of using Stockholm3 test to select men for further workup using MRI followed by targeted biopsies and systematic biopsies compared to using PSA followed by systematic biopsies (i.e. testing the overarching primary hypothesis of the trial). Sensitivity analyses will include contrast of Strategy 5 vs. 2 and Strategy 5 vs. 1. In addition, for the contrast of Strategy 6 vs. 1, we will – if Stockholm3  $\geq 11\%$  is more sensitive than PSA  $\geq 3$  – also report results at the operating point of Stockholm3 (i.e. the Stockholm3 cutoff) that gives equal sensitivity as PSA  $\geq 3$  within the experimental arm (analogously to how we performed the STHLM3 trial, see Grönberg et al.), see the “Additional analysis” section in this document for more information.

This comparison is motivated by the fact that MRI+targeted biopsy will be used more and more frequently, with the possibility of them eventually replacing systematic biopsies as the de-facto standard diagnostic tool. For example, the National Institute for Health Care and Excellence (NICE) in the UK already recommends MRI as “the first-line investigation for people with suspected clinically localised prostate cancer”. Therefore, we aim to compare the Stockholm3 test with the PSA test – in terms of sensitivity (ISUP $\geq 2$ ), specificity (ISUP1), number of biopsies and number of MRI scans – as a tool to select men for further workup, as well as compare the entire diagnostic chain of using Stockholm3 followed by MRI and TBx+SBx to the traditional diagnostic chain of using PSA followed by SBx (for which there exists level 1 evidence of reduced prostate cancer specific mortality when used for prostate cancer screening (Schröder et al. 2009 and 2014)). Publication 2 will cover the primary overarching hypothesis, as well as additional hypotheses 3 and 4.

Another way to motivate the order of these two publications is that the first publication will assess whether MRI and TBx+SBx improves diagnostic accuracy in a population based

 As also pointed out in by [name] and [name] in the review of the study protocol [Nordström et al, BMJ Open 2019]. The comments are now available at the journal's website.

 See <https://www.nice.org.uk/guidance/NG131/chapter/recommendations#multiparametric-mri-and-protocol-for-active-surveillance>

screening-by-invitation setting, as it seems to do in clinical cohorts (Kasivisvanathan et al. and Ahdoot et al., Rouvière et al., and Grönberg et al.), whereas the second publication will assess whether Stockholm3 can improve selection of men to undergo MRI (an key point since MRI is an expensive and scarce resource and population-based screening involving MRI will lead to large number of MRI examinations).

The results presented in Publications 1 and 2 will thus together cover the testing of the overarching primary hypothesis, as well as additional hypothesis 1, 2, 3, 4, and 5.

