#### *Contrasts between study arms (unpaired design)*

Analyses will compare the difference in detection probabilities (DPs) between study arms. The DP is the probability of being endpoint-positive given the study arm and, possibly, either or both screening tests being positive. For example the DP of ISUP1 in men randomised to the experimental arm and Stockholm3-positive is equal to  $\Pr(\text{ISUP1} \mid \text{Stockholm3} \geq 11\%, \text{Experimental arm})$ .

**Absolute scale.** The absolute difference in DPs is defined as the DP in the experimental arm minus the DP in the standard arm ( $\Delta\text{DP} = \text{DP}_{\text{Exp}} - \text{DP}_{\text{Std}}$ ) or vice versa, as appropriate. It is estimated by plugging into the formula the observed proportions. An approximate 100(1- $\alpha$ )% two-sided Wald confidence interval for  $\Delta\text{DP}$  is calculated as

$$\widehat{\Delta\text{DP}} \pm z_{\alpha/2} \sqrt{\frac{\widehat{\text{DP}}_{\text{Exp}}(1-\widehat{\text{DP}}_{\text{Exp}})}{n_{\text{Exp}}} + \frac{\widehat{\text{DP}}_{\text{Std}}(1-\widehat{\text{DP}}_{\text{Std}})}{n_{\text{Std}}}}.$$

**Relative scale.** The relative difference in DPs is defined as the DP in the experimental arm divided by the DP in the standard arm ( $r\text{DP} = \text{DP}_{\text{Exp}}/\text{DP}_{\text{Std}}$ ) or vice versa, as appropriate. It is estimated by plugging into the formula the observed proportions. An approximate 100(1- $\alpha$ )% two-sided Wald confidence interval for  $r\text{DP}$  is calculated as

$$\exp\left(\log(\widehat{r\text{DP}}) \pm z_{\alpha/2} \sqrt{\frac{1}{\widehat{\text{DP}}_{\text{Exp}} * n_{\text{Exp}}} - \frac{1}{n_{\text{Exp}}} + \frac{1}{\widehat{\text{DP}}_{\text{Std}} * n_{\text{Std}}} - \frac{1}{n_{\text{Std}}}}\right).$$

Contrasts 3 vs 1, 2 vs 1, and 9 vs 7 will be analysed using absolute differences (Study 1). Contrasts 6 vs 1, and 5 vs 1 will be analysed using relative differences (Study 2).

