| 0.020 | 0.61 | 0.67 |
| 0.025 | 0.61 | 0.77 |
| 0.030 | 0.61 | 0.84 |
| 0.015 | 0.63 | 0.59 |
| 0.020 | 0.63 | 0.71 |
| 0.025 | 0.63 | 0.80 |
| 0.030 | 0.63 | 0.87 |

2. More than 90% power for the contrast PSA+MRI+TBx+SBx vs PSA+SBx (rDP = 1.3, noninferiority margin for  $\Delta DP \delta = 0.04$ ,  $\alpha = 0.025$ ).

Thus, contrast 1 drives the required samples size of the study. We therefore powered the study (with respect to sample size for sending out invitations and enrolling participants) to have sufficient statistical power to answer comparisons of Stockholm3 vs. PSA within the experimental arm.

Note: no correction for multiple comparisons was made. This means that each of the three tests (with respect to the ISUP 2, ISUP 1, and biopsy endpoints) has an approximate type I error rate of 2.5% if the corresponding null hypothesis is true. If all three null hypotheses are true and we assume the tests to be independent, the overall type I error rate is approximately 7%. In reality however, these hypotheses are strongly correlated. Thus, the overall type I error rate is bounded below by 2.5% and above by 7%.

R code for the power calculations is available at:

<https://gist.github.com/anddis/fc1a265d102b509b0eacd59ab065661a>

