### Additional analyses

Due to updates in the Stockholm3 assay system to reduce measurement errors in the biomarkers included in the Stockholm3 risk prediction model, Stockholm3  $\geq 11\%$  as a selection criterion for randomization may be more sensitive than PSA  $\geq 3$  (i.e. more men with clinically significant prostate cancer will be randomized based on the criterion Stockholm3  $\geq 11\%$  compared with PSA  $\geq 3$ ). If this turns out to be true, we will perform analyses where we “count backwards” (increase the S3M cutoff) and compare biopsy rates at identical sensitivity for clinically significant prostate cancer when comparing diagnostic strategies involving S3M compared with PSA  $\geq 3$  (as described in Grönberg et al.).

We will artificially randomise (2:3) those men who screened negative on both screening tests. By doing this, the totals [d]+[h] and [d']+[h'] will become known, which in turn will allow the estimation of quantities like  $\Pr(\text{ISUP} \geq 2, \text{Stockholm3} \geq 11\% \mid \text{Standard arm})$  (i.e., the probability of ISUP  $\geq 2$  and Stockholm3  $\geq 11\%$  in enrolled men randomised to the standard arm). Contrasts between the two study arms with respect to these quantities will be

---

 Where applicable.

performed using the same methodology described in the section “Contrasts between study arms (unpaired design)”.

We may in additional analyses use regression models to model the DP, TPF, and FPF given covariates. We will employ standard generalised linear models or marginal models (Pepe and Alonzo 2001), as appropriate.

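### The Stockholm3 cut-off matched to PSA ≥3 inside the MRI arm is reported for Strategy 6 vs 1, where it does not give the equal-sensitivity comparison the SAP describes

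*Combined protocol and SAP*

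**What the plan says.** The SAP's publication strategy (Publication 2) introduces the analysis with "In addition, for the contrast of Strategy 6 vs. 1, we will" and makes it conditional on Stockholm3 ≥11% being more sensitive than PSA ≥3. The SAP will then "also report results at the operating point of Stockholm3 (i.e. the Stockholm3 cutoff) that gives equal sensitivity as PSA" ≥3. The match is made "within the experimental arm (analogously to how we performed the STHLM3 trial" and so on, and the reader is sent to Additional analyses for detail.

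Additional analyses gives the purpose: to "compare biopsy rates at identical sensitivity for clinically significant prostate cancer when comparing diagnostic strategies involving S3M compared with PSA" ≥3. It names no arm and no strategy numbers.

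Under Design, Strategy 1 is PSA+SBx, Strategy 3 is PSA+MRI+TBx+SBx and Strategy 6 is S3M+MRI+TBx+SBx. Contrasts between study arms puts 6 vs 1 on the relative scale and 3 vs 1 on the absolute scale. It defines the detection probability (DP) loosely: "The DP is the probability of being endpoint-positive given the study arm and, possibly, either or both screening tests being positive". The next section reads a ratio of DPs as a relative sensitivity.

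**The concern.** The cut-off is matched to one strategy and the result is reported against another. PSA ≥3 within the experimental arm is Strategy 3. Strategy 1 differs from it by the whole MRI step, and the SAP assumes that step changes detection of ISUP ≥2 cancer. A cut-off that equalises Strategies 6 and 3 therefore does not equalise Strategies 6 and 1.

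What is at stake is interpretation. The ISUP ≥2 figure for 6 vs 1 at this cut-off would reflect MRI-based against systematic biopsy, in a paper that also asks whether Stockholm3 selects men better than PSA. The biopsy rate beside it would be described as an equal-sensitivity result when it is not one.

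**Working it through.** **Inputs**

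- ISUP ≥2 rate with SBx in men with PSA ≥3: 18%. Ratio for MRI+TBx vs SBx: 1.25 (SAP, Basic data and assumptions).
- Ratio for 3 vs 1: 1.3. Absolute margin 0.04, α 0.025 (SAP, Updated sample size calculations).
- About 1,600 randomised men with PSA ≥3, 20% drop-out, about 1,700 men completing the diagnostic chain (same section); allocation 2:3.
- Cell labels from SAP, Data structure. For ISUP ≥2, a+c counts cancers in PSA-positive men in the standard arm; primes mark the experimental arm.

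**The plan's own figure.** The SAP states "More than 90% power for the contrast PSA+MRI+TBx+SBx vs PSA+SBx". Completers with PSA ≥3: 1,600 × 0.8 = 1,280, split 512 and 768. Rates: 0.18 and 0.18 × 1.3 = 0.234.

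SE = √(0.18×0.82/512 + 0.234×0.766/768) = 0.0228

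Power = Φ((0.054 + 0.04)/0.0228 − 1.96) = 98.4%, which agrees.

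**Step 1: the identity.** Let X′(k) be the number of ISUP ≥2 cancers in experimental-arm men with Stockholm3 ≥k. Matching within that arm picks k* so that X′(k*) = a′+c′, up to ties in the score. With N and N′ men randomised to the standard and experimental arms:

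rDP(6 at k* vs 1) = [X′(k*)/N′] / [(a+c)/N] = [(a′+c′)/N′] / [(a+c)/N] = rDP(3 vs 1)

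Stockholm3 has dropped out of the ISUP ≥2 ratio.

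**Step 2: size.** Per 1,000 men with PSA ≥3 in each arm, Strategy 1 finds 180 cancers. Strategy 3, and so Strategy 6 at k*, finds 180 × 1.25 = 225 to 180 × 1.3 = 234. At planned size with ratio 1.3, expected cancers are 0.18 × 512 = 92.2 and 0.234 × 768 = 179.7, among 1,700 × 0.4 = 680 and 1,700 × 0.6 = 1,020 men. The SAP's interval formula gives 1.30 (95% CI 1.03 to 1.64) for both contrasts. For Strategy 6 to match Strategy 1, the cut-off would need a within-arm ratio to PSA of 1/1.25 = 0.80 or 1/1.3 = 0.77, not 1.

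**Step 3: the conditional form.** If DP is taken among test-positive men, the 6 vs 1 ratio becomes 1.3/f, where f is the number of men above k* divided by the number with PSA ≥3. The documents do not give f. Assuming f from 1.0 to 0.5, the ratio runs from 1.3 to 2.6. This is not a sensitivity ratio: the two arms are conditioned on different tests, so the prevalence terms that cancel in SAP Appendix 1 no longer do.

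**Step 4: biopsies, by illustration.** The correlations between PSA, Stockholm3 and cancer are not in the documents, so they were assumed in a simulation. It used 12,500 men, 13% PSA-positive, a detection ratio of 1.3, and MRI-arm biopsy in 45% of men plus every man with a detectable cancer. Its control-arm ISUP ≥2 rate was 14.6%, below the plan's 18%. In the 473 of 500 trials where the trigger was met, mean biopsy rates relative to Strategy 1 were:

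| Strategy | Relative biopsy rate |
|---|---|
| 3 | 0.554 |
| 6 at k* | 0.445 |
| 6 at a cut-off matched to Strategy 1 | 0.312 |

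The per-randomised-man ISUP ≥2 ratios for 6 at k* vs 1 and for 3 vs 1 were identical in every trial, as Step 1 requires. From the averages, 6 at k* vs 3 is 0.445/0.554 = 0.80: about 20% fewer biopsies than Strategy 3, against about 55% fewer than Strategy 1.

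**The case against.** The strongest defence is that the SAP says openly where the match is made. One may fix the blood test at PSA's sensitivity and then describe the whole chain against PSA+SBx. That is coherent, provided the result is labelled that way. It does not supply the identical sensitivity that Additional analyses gives as the purpose.

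Several stronger readings are tempting, and the documents do not support them.

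- **A non-inferiority claim at this cut-off would be carried by MRI.** Neither section plans a test there; the results are reported additionally and the stated aim is biopsy rates.
- **Strategy 6 vs 3 is left out.** The matched cut-off is not attached to it in Publication 2, but the wording in Additional analyses is general and does not exclude it.
- **Publication 1's result is simply printed again.** Publication 1 uses an absolute difference with margin 0.04, while 6 vs 1 uses a ratio with margin 0.78. The identity holds on the per-randomised-man scale, not for the conditional DP. Biopsy, MRI and ISUP 1 counts at k* still depend on Stockholm3.
- **Mixing MRI and Stockholm3 effects is an error.** Assessing the entire chain is the stated purpose of 6 vs 1.
- **The saving is inflated.** On the plan's ratios it is understated as an equal-sensitivity saving.

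**Conclusion.** The concern holds as a mismatch between the matching target and the reported contrast. For 6 vs 1 at k*, sensitivity is not equal: on the plan's assumptions Strategy 6 detects 25 to 30% more ISUP ≥2 cancers than Strategy 1, and that excess is the 3 vs 1 effect, with no information on Stockholm3. This rests on the per-randomised-man DP, the form in which 6 vs 1 can be read as a relative sensitivity.

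The direction depends on MRI. If it detects more cancers, as the plan assumes, the biopsy saving is obtained at higher sensitivity than Strategy 1 (illustratively a relative biopsy rate of 0.45, against 0.31 at a true match). If it detects fewer, the saving is at lower sensitivity and overstated. Equality holds only if the 3 vs 1 ratio is 1.

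The analysis is additional and conditional. The main 6 vs 1 test at Stockholm3 ≥11% is untouched, and the match is valid for 6 vs 3. The change should be made, but the fault does not threaten the trial's primary conclusion.

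**What to change.** In both Publication 2 and Additional analyses, attach the within-arm matched cut-off explicitly to Strategy 6 vs 3. Report MRIs, biopsies and ISUP 1 cancers at equal ISUP ≥2 detection in the same men, with no ISUP ≥2 test because equality is built in.

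If 6 vs 1 is also shown at that cut-off:

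- label it as matched to PSA ≥3 within the MRI arm;
- show the ISUP ≥2 ratio alongside the biopsy rate, and state that it is per randomised man;
- do not call it equal sensitivity, and draw no ISUP ≥2 conclusion about Stockholm3 from it.

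The cost is SAP wording and one table. Re-matching the cut-off to Strategy 1 across arms is possible but is a trade-off: it is less precise, it makes the ISUP ≥2 ratio 1 by construction, and on the plan's ratios it requires a within-arm ratio to PSA of 0.77 to 0.80, around the plan's own 0.78 margin.

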## Aims and endpoints

The primary aim and key secondary aims of this trial are described below (corresponding with the overarching primary hypothesis and additional hypothesis 1-4 above), together with definitions of study variables (independent variables and outcome variables). A description of how and on which data statistical testing will be performed is specified in the Statistical Analysis section.

### Primary aim

To test whether a diagnostic pathway using the Stockholm3 test to select men for further workup using MRI followed by targeted biopsies and systematic biopsies (Strategy 6; S3M+MRI+TBx+SBx) has non-inferior sensitivity for detecting clinically significant cancer (ISUP grade  $\geq 2$ ) and shows superior specificity (reduction in number of performed biopsy procedures and detected ISUP 1 tumours) compared with the diagnostic pathway using systematic biopsies in men with PSA  $\geq 3$  ng/mL (Strategy 1; PSA+SBx).

### Key secondary aims

1. To test whether targeted prostate and systematic biopsies performed in MRI positive men will lead to: non-inferior sensitivity for detecting clinically significant cancer (ISUP grade group  $\geq 2$ ); reduced number of performed biopsy procedures; and lower proportion of men with elevated risk who experience severe post-biopsy infections compared to systematic biopsies for men with elevated risk (defined as being positive on PSA and/or Stockholm3) of prostate cancer in prostate cancer screening.
2. To test whether targeted prostate biopsies performed in MRI positive men will lead to: non-inferior sensitivity for detecting clinically significant cancer (ISUP grade  $\geq 2$ ); reduced number of performed biopsy procedures; and lower proportion of men with elevated risk who experience severe post-biopsy infections compared to systematic biopsies for men with elevated risk (defined as being positive on PSA and/or Stockholm3) of prostate cancer in prostate cancer screening.
3. To test whether a diagnostic chain consisting of Stockholm3 followed by MRI and targeted+systematic biopsies versus a diagnostic chain based on PSA  $\geq 3$  ng/ml followed by MRI and targeted+systematic biopsies will lead to: non-inferior sensitivity for detecting clinically significant cancer (ISUP grade group  $\geq 2$ ); an inferior sensitivity for ISUP1 cancers (i.e. reduced overdiagnosis); and a reduction in the number of MRI examinations and performed biopsies.
4. To test whether a diagnostic pathway using the Stockholm3 test to select men for further workup using MRI followed by ONLY targeted biopsies (S3M+MRI+TBx) has non-inferior sensitivity for detecting clinically significant cancer (ISUP grade  $\geq 2$ ) and reduces the number of performed biopsy procedures compared with a diagnostic pathway using systematic biopsies in men with PSA  $\geq 3$  ng/mL (PSA+SBx).

